# The effects of green cardamom supplementation on blood glucose, lipids profile, oxidative stress, sirtuin-1 and irisin in type 2 diabetic patients: a study protocol for a randomized placebo-controlled clinical trial

**DOI:** 10.1186/s12906-017-2068-6

**Published:** 2018-01-17

**Keywords:** Trial protocol, Diabetes, Green cardamom

## Abstract

**Background:**

It has been suggested that the antioxidant, anti-inflammatory and hypolipidemic activities of cardamom may improve diabetes. However, the effect of this spice has not been investigated in diabetic subjects. This study was planned to determine the effects of green cardamom on blood glucose, lipids and oxidative stress status in type 2 diabetic patients.

**Methods/design:**

Eighty overweight or obese patients with type 2 diabetes will be selected. They will be randomly assigned to receive 3 g/d green cardamom or placebo for 10 weeks. The socio demographic, physical activity and 24-h food recall questionnaires will be collected for each subject. Weight, height and waist circumference will be measured. Determination of blood glucose, lipid profile, and oxidative stress biomarkers including serum levels of total antioxidant capacity (TAC), malondialdehyde (MDA), and glutathione peroxidase (GPx) and superoxide dismutase (SOD) in red blood cells will be performed. The homeostasis model assessment-estimated insulin resistance **(**HOMA**-**IR**)** index and the quantitative insulin-sensitivity check index (QUICKI) will be calculated. Also, serum levels of irisin, and Sirtuin1 (SIRT1) will be measured.

**Discussion:**

This trial will be the first study to explore the effects of green cardamom supplementation on glycemic control, lipid profile and oxidative stress in patients with type 2 diabetes mellitus. The results from this trial will provide evidence on the efficacy of green cardamom in type 2 diabetes mellitus.

**Trial registration number:**

(http://www.irct.ir, identifier: IRCT2016042717254N5), Registration date: 23.11.2016.

## Background

Diabetes Mellitus (DM) is a non-communicable disease that affects many persons annually. In 2000, 171 million people suffered fromDM globally, and it has been estimated to reach 366 million people in 2030 [1]. DM increases the risk of cardiovascular disease (CVD) by 2 to 4-fold. Dyslipidemia plays an important role in the pathogenesis of CVD in type 2 diabetes mellitus (T2DM) patients [2].

Studies have shown that high glucose level by stimulating reactive oxygen species (ROS) production damages β-cells and leads to impaired insulin release and insulin resistance [3, 4]. The antioxidant defence system is responsible for the neutralization of ROS; however, β-cells have a poor antioxidant defence system. Therefore, antioxidant supplementation by elevating antioxidant defence capacity can protect against β-cells dysfunction [5].

Many investigations have been executed regarding the relationship between sirtuin-1 (SIRT1) and irisin with the occurrence of DM. SIRT1 is a class III protein deacetylase that is associated with aging, inflammation and CVD [6]. Moreover, it has been suggested that SIRT1 plays an important role in glucose metabolism by stimulating pancreatic insulin release and insulin signaling pathway [7]. Investigations have stated that activation of SIRT1 leads to deacetylation of nuclear factor (NF)-κB, peroxisome proliferator activated receptor (PPAR)-γ and PPAR-γ coactivator 1α (PGC-1α) which have beneficial effect on glycemic indices, obesity and mitochondrial function [6, 7]. PGC-1α is a transcriptional coactivator that regulates energy balance and expression of fatty acids oxidation genes. In addition, it is involved in the improvement of mitochondrial function, insulin sensitivity and alleviation of oxidative stress. PPAR-γ and NF-κB are transcriptional factors that regulate fat metabolism and inflammation, respectively. Therefore, the inhibition of PPAR-γ and NF-κB activity by SIRT1 deacetylation suppresses fat accumulation and inflammatory processes in the human body [6, 8]. Studies have shown that lower SIRT1 activity is involved in the pathogenesis of DM and insulin resistance. Therefore, interventions that increase SIRT1 activity may be beneficial in improvement of insulin resistance and control of DM [7, 8]. Studies have shown that dietary polyphenols by stimulation of SIRT1 activity result in the suppression of NF-κB and activation of PGC-1α; hence improving insulin resistance and lipid metabolism [6].

Irisin is a recently known exercise-mediated myokine that regulates glucose hemeostasis [9]. Irisin contributes to the browning of white adipose tissue by increasing uncoupling protein-1 (UCP-1) in these cells, which results in the improvement of insulin sensitivity and glucose metabolism. UCP-1 is a key molecule that regulates energy expenditure [10]. Studies have indicated that a lower level of irisin is associated with DM and insulin resistance [9]. The activation of PGC-1α is the main stimulator of irisin release, therefore the elevation of irisin level may be a therapeutic approach in the management of insulin resistance and DM. It has been suggested that flavonoids such as quercetin and resveratrol by activation of PGC-1α- and the SIRT1-related signaling pathway contribute to mitochondrial biogenesis [11]. Mitochondria regulates oxidative metabolism in muscle, hence increase in mitochondrial biogenesis results in higher insulin-related glucose uptake by muscle which subsequently improves insulin sensitivity [12].

Green cardamom (*Elettaria cardamomum*) is a dietary spice (in the ginger family) with nutraceutical effects that has antioxidant, anti-inflammatory and anti-carcinogenic properties [13, 14]. In a recent study, Ahmed et al. indicated that cardamom supplementation by supression of α-amylase and α-glucosidase enzymes has anti-diabetic effects and may regulate glucose metabolism [15]. Cardamom volatile oil is composed of terpenes, esters, flavonoids, 1,8-cineole, alpha-terpinyl acetateand limonene [16]. Previous studies have indicated that 1,8-cineole has antioxidant and lipid-lowering effects [17, 18]. Cardamom is high in polyphenolic compounds such as quercetin, kaempferol, luteolin and pelargonidin which possess antioxidant properties [19]. It has been reported that resveratrol and quercetin can increase the deacetylation effect of SIRT1 by 13-fold and 4.6-fold, respectively [20]. Therefore, it has been hypothesized that cardamom antioxidant and anti-inflammatory activities may improve DM. Kandikattu et al. in an experimental model has shown that cardamom can stimulate in vitro superoxide dismutase (SOD), catalase and glutathione activity [21]. However, in two randomized clinical trials, cardamom (3 g/d) had no significant effect on oxidatve stress biomarkers in pre-diabetic and diabetic patients [22, 23]. To the best of our knowledge, there is no clinical trial that has investigated the effects of cardamom on SIRT1 secretion and subsequently PGC-1α, irisin and insulin sensitivity in diabetic patients. Therefore, this study has designed to investigate the effect of *Elettaria cardamomum* on blood glucose, lipid profile and oxidative stress biomarkers in T2DM patients. To determine the mechanism of cardamom effect on blood glucose and lipid levels, blood irisin, and SIRT1 will be assessed.

## Methods and design

### Study design

This is a randomized, double blind, clinical trial. The flow chart of the study protocol is presented in Fig. 1. This study was conducted at the Diabetes Research Center, Endocrinology and Metabolism Clinical Sciences Institute, Tehran University of Medical Sciences, Tehran, Iran.

**Fig. 1 Fig1:**
[figure not shown]
Participants flow diagram

### Sample size:

The sample size was calculated using the following equation:$$ n=\frac{{\left({Z}_{1-\alpha /2}+{Z}_{1-\beta}\right)}^2\left({S}_1^2+{S}_2^2\right)}{{\left({\mu}_1-{\mu}_2\right)}^2} $$

A total of 40 diabetic patients were calculated in each group (cardamom and placebo groups) based on a significant mean difference of TAC [24], with 95% confidence level, 80% power and additional drop-out rate of 20%.

### Study population

T2DM patients were recruited from the outpatient department of Diabetes Research Center, Endocrinology and Metabolism Clinical Sciences Institute, Tehran University of Medical Sciences, Tehran, Iran. The diagnosis of diabetes will be based on medical records, using the American Diabetic Association (ADA), (fasting blood sugar (FBS) ≥126 mg/dl or 2-h postparndial (2HP) ≥ 200 mg/dl or HbA1c ≥6.5%) [25]. Eligible diabetic patients will be enrolled in the study and written informed consent was obtained at the baseline.

### Inclusion and exclusion criteria

For the present study, T2DM patients, aged 30–60 years, with a diagnosis of T2DM for at least 2 years, HbA1C value greater than 7%, body mass index (BMI) between 25 and 35 kg/m^2^, who will be treated with a stabilized dose of oral anti-diabetic drugs and statins will be included in the study.

Patients will be excluded if: 1) they are pregnant or lactating; 2) have gastrointestinal disorders that interfere with the bowel function, severe hepatic, renal (dialysis), inflammatory and thyroid diseases; 3) being on insulin therapy or need insulin based on expert physician’s opinion 4) have diabetes complications including micro and macrovascular complications; 5) take warfarin, fibrates (PPAR- α ligand), TZD (PPAR- gammaligand) and anti-depressant agents; 6) adhering to a specific diet during the past 3 months; 7) have history of smoking or alcohol intake at least once a week in the past month; 8) receive (at least once a week) herbals, antioxidant, multivitamin/mineral supplements in the past 3 months; 9) they were unstable on the current dose of medications. Patients, who consume less than 90% of their intervention, will also be excluded.

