##### Statistical analysis

All statistical analyses will be performed using SPSS version 21 (SPSS Inc., Chicago, USA). Data will be expressed as mean ± SD for continuous variables and percentage for non-continuous variables. Normality tests will be assessed through Shapiro-Wilk tests carried out on each parameter before analysis. All outcome variables will be assessed based on intention-to-treat and per protocol analysis. Missing data will be entered using “regression imputation” method. To compare the mean differences between the two groups, the independent *t*-test and Mann–Whitney will be used for normal and non-normal data respectively, considering the normality of data. A multivariate repeated-measures regression analysis will be used to assess time effects and time-by-treatment interactions effect on all outcome variables. A *p*-value of less than 0.05 will be considered as significant.

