## Ethical considerations

This clinical trial will be conducted after approval by the Ethics Committee of Tehran University of Medical Sciencesand after obtaining informed consent from the participants. Whenever a person is unable to continue supplementation, he/she will be excluded from the study.

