## The limitations

One of the limitations of this study is the lack of cooperation of some patients who were replaced with other patients.

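### Excluding randomised patients for low capsule intake or for stopping supplementation contradicts the promised intention-to-treat analysis

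*Protocol article*

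**What the plan says.** Under Statistical analysis the article states: "All outcome variables will be assessed based on intention-to-treat and per protocol analysis". For gaps in the data it adds: "Missing data will be entered using “regression imputation” method".

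Three other sections bear on who is left to analyse:

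- Inclusion and exclusion criteria, directly after the list of eligibility exclusions: "Patients, who consume less than 90% of their intervention, will also be excluded".
- Ethical considerations: "Whenever a person is unable to continue supplementation, he/she will be excluded from the study".
- The limitations names as a limitation "the lack of cooperation of some patients who were replaced with other patients".

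The Sample size section arrives at 40 patients per group and already includes a 20% allowance for drop-out. The Procedure section has two clinic visits, at baseline and after 10 weeks. Patient safety provides for weekly monitoring and recording of adverse events.

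**The concern.** An intention-to-treat analysis keeps every randomised patient in the assigned group, whatever happens later. Capsule intake and the ability to continue are later events. Rules that exclude on them leave a comparison of patients selected for adherence, and randomisation no longer guarantees that the two groups are alike. The arms swallow different substances (cardamom or rusk powder), so the reasons for stopping could differ between them.

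The rules act on every primary outcome at once. A week-10 blood sample that was not taken cannot be recovered afterwards. If the intention-to-treat result for patients who stopped is filled in from those who stayed, it also loses much of its value as a check on the per-protocol result.

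**Working it through.** **1. Are the exclusions post-randomisation?** Inputs from Intervention: 0.5 g per capsule, 3 g per day, 10 weeks.

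- Capsules per day: 3 / 0.5 = 6.
- Total: 6 × 70 days = 420.
- 90% threshold: 0.9 × 420 = 378.

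Whether a patient reaches 378 can be known only once dosing is under way; the article counts returned capsules monthly. Being unable to continue likewise presupposes having started. Neither rule can work as an eligibility criterion.

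**2. The sections side by side.**

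| Section | Whom it affects | Limited to the per-protocol set? |
|---|---|---|
| Inclusion and exclusion criteria | intake below 90% | not stated |
| Ethical considerations | those who stop | no; excluded from the study |
| The limitations | uncooperative patients, replaced | timing not stated |
| Statistical analysis | all outcomes, by intention to treat and per protocol | both sets promised |

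No section says that excluded patients are followed to week 10 or kept in their randomised group.

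**3. The plan's own sample size.** The 40 per group cannot be reproduced, because the article gives neither the difference in total antioxidant capacity nor its SDs. Working backwards, 32 / (1 − 0.20) = 40. With two-sided 5% significance and 80% power, the article's formula gives a standardised difference of

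d = √2 × (1.960 + 0.842) / √32 = 0.70.

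(If the allowance was instead applied as 33 × 1.20 = 39.6, rounded up to 40, d = 0.69.) The 0.70 is therefore implied, not stated.

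**4. Illustration of dilution.** Assumptions: adherers gain 0.70 SD; a share q = 0.20 stops and gains nothing; those who stop do not otherwise differ in prognosis.

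- Intention-to-treat effect: (1 − q) × 0.70 = 0.8 × 0.70 = 0.56 SD.
- Analysis of adherers: about 0.70 SD.
- Ratio: 0.70 / 0.56 = 1.25.

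Imputing those who stop from adherers of the same arm also returns about 0.70 SD. The article does not say whether its imputation model contains the arm.

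**5. Illustration under no true effect.** Simulation of 5,000 trials per row, 40 randomised per arm. Each patient has an adherence score correlated with outcome, and the least adherent share of each arm is removed. All settings are assumptions.

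| Removed, arm A / arm B | Correlation | Bias (SD) | Type I error |
|---|---|---|---|
| 20% / 20% | 0 | 0.000 | 5.0% |
| 20% / 20% | 0.5 | 0.004 | 4.9% |
| 25% / 15% | 0.3 | 0.045 | 5.4% |
| 25% / 15% | 0.5 | 0.073 | 6.0% |
| 30% / 10% | 0.3 | 0.084 | 5.9% |
| 30% / 10% | 0.5 | 0.150 | 9.5% |

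Equal removal gives essentially no bias. Bias needs removal that differs by arm and is related to outcome.

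**6. Is replacement needed for power?** Power = Φ(d√(n/2) − 1.96). At d = 0.70, 32 per arm gives 80% and 40 measured per arm gives 88%. The 20% allowance therefore already covers lost measurements. It does not cover dilution: at 0.56 SD with 40 per arm, 0.56 × √20 − 1.96 = 0.54, which is a power of about 71%.

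**The case against.** The best defence is that a compatible reading exists. Planning two analysis sets and an imputation step makes sense only if some randomised patients fall outside the per-protocol set but stay in the intention-to-treat set. A 90% intake threshold is a usual per-protocol definition, the article offers no other, and an article may leave exact set definitions to a fuller document. On this reading the 90% sentence is merely misplaced. That is plausible for the 90% rule, although its section does not say so. It is hard to sustain for the Ethical considerations sentence, which excludes from the study and not from one analysis. The article is not silent here; it states rules that conflict.

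The defence is right against several stronger inferences that a reader might draw:

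- **That replacement broke the randomised comparison.** The limitations section gives no timing; patients may have withdrawn before allocation. Only replacement after randomisation would add to the problem.
- **That intention to treat collapses onto per protocol for everyone excluded.** No section says that week-10 samples are missing. For the group below 90% this is doubtful, since full intake is known only at the end, when the week-10 visit takes place. The argument is stronger for those who stop, and even there it is conditional.
- **That patients with adverse effects vanish from the safety data.** Adverse events are recorded weekly, and nothing says that events before exclusion are discarded.
- **That a 25% overstatement has been shown.** It needs the implied 0.70 SD, the drop-out allowance reused as the share who stop, and zero effect in all of them. A patient at 89% intake would also be excluded, and zero effect there is an extreme assumption.

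**Conclusion.** The contradiction stands on three sections alone: the 90% exclusion and the exclusion of those who stop cannot both be followed literally alongside an intention-to-treat analysis. The replacement statement is a separate ambiguity to be cleared up, and the point does not depend on it.

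The size of any bias is unknown. Under the stated assumptions the contrast is 0.56 SD against about 0.70 SD. With no true effect, the simulated bias ranges from essentially none (equal exclusion) to 0.15 SD with 9.5% type I error (30% against 10% removed, correlation 0.5). These figures show the direction and the conditions; they do not predict this trial. The point still needs correcting before analysis, because the rules decide who is analysed for every primary outcome and missed week-10 measurements cannot be recovered.

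**What to change.** 1. Move the 90% threshold out of the exclusion criteria and use it only to define the per-protocol set.
2. Reword the Ethical considerations sentence so that patients who stop capsules remain in follow-up and have the planned week-10 blood sample and measurements. This concerns data collection only and leaves open when a patient should stop.
3. Make the analysis of all randomised patients, in their assigned groups, the main analysis, with per protocol as supportive.
4. State that randomised patients are not replaced. The article reports replacement in the past tense, so where it happened after randomisation, report number, arm and timing, and keep the replaced patients in the intention-to-treat set. If it happened only before randomisation, say so.
5. State that adverse events recorded before a patient stops are included in the safety summary.

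The cost is protocol wording, effort to bring patients who stopped to a visit that is already planned, and a look back at the replacement records. The downside is that the estimated effect, and with it the power, may be somewhat smaller than in an analysis of adherers.

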### Randomization

Participants will be randomly allocated into two groups: cardamom and placebo groups and will be followed-up for 10 weeks. Randomizations will be conducted by an assistant using permuted block randomization method and stratified randomization will be used to match participants based on age and gender distribution. The intervention allocation will be blinded for both investigators and participants.

### Intervention

Fruits of *Elettaria Cardamom* will be purchased from Samex Agency (India), by the Traditional Medicine and Research Centre (TMRC), Shahid Beheshti University of Medical Sciences, Tehran, Iran. Cardamom (green cardamom powder) and placebo (rusk powder) capsules will be prepared by TMRC. Each capsule will contain 0.5 g of whole green cardamom powder or rusk powder. Shape, size and color of placebo capsules will be completely similar to the cardamom capsules. All placebo capsules will be placed in the same bag containing the cardamom capsules, in order to have the smell of cardamom.

The voucher number of green cardamom is *E. cardamomum* (L.)Maton, Family: Zingiberaceae, PMP-669. Essential oil, as well as the phenolic and flavonoid contents of whole green cardamom will be measured using gas chromatography–mass spectrometry (GC-MS) and high-performance liquid chromatography (HPLC) at the Institute of Medicinal Plants, Shahid Beheshti University of Medical Sciences. Some of the polyphenolic compounds of green cardamom such as caffeic acid, gallic acid, quercetin and luteolin, which were mentioned in other articles [26, 27] will be determined by HPLC. Cardamom and placebo capsules will be provided to both groups monthly for 10 weeks. Participants will be required to consume 2 capsules (3 g daily) per meal. The last packages of capsules will be checked at the end of the month and the number of remaining capsules will be counted; thereafter, new packages will be delivered to patients. All capsules will be given simultaneously with the usual diabetes care that includes maintenance of the oral anti-diabetic drugs dosage.

Participants will be asked to keep their usual lifestyle including medical nutrition therapy and physical activity level.

### Adherence

To assess patients’ compliance during the 10 weeks, a researcher will be assigned to check them weekly using telephone to discern whether they were consuming the supplements.

### Patient safety

Patients will be monitored weekly during the study period and any occurrence of adverse events will be recorded.

#### Study outcomes

##### Primary outcomes

The primary outcomes of this clinical trial are the changes in HbA1C, FBS, insulin, lipid profile (triglyceride, total cholesterol, HDL-cholesterol, LDL-cholesterol), oxidative stress biomarkers such as TAC, SOD, GPx, MDA, SIRT1 and irisin at the end of the study in comparison with the baseline values.

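### Thirteen primary outcomes with no lead, order or success rule share one p<0.05 threshold, so type I error over the primary family is not controlled; the 5% level and 80% power belong to TAC alone

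*Protocol article*

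**What the plan says.** The Primary outcomes section of the protocol article opens with "The primary outcomes of this clinical trial are the changes in HbA1C, FBS, insulin, lipid profile". It spells out the lipids as "triglyceride, total cholesterol, HDL-cholesterol, LDL-cholesterol" and ends with "oxidative stress biomarkers such as TAC, SOD, GPx, MDA, SIRT1 and irisin". All are changes from baseline to the end of the study. Only weight, BMI and waist circumference are secondary.

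The Statistical analysis section compares the groups by t-test or Mann-Whitney test, adds a repeated-measures regression on all outcome variables, and uses both intention-to-treat and per-protocol sets. It closes with one rule: a p-"value of less than 0.05 will be considered as significant". It gives no hierarchy and no adjustment, and it does not describe the regression as a global or gatekeeping test.

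The Sample size section sets 40 per group "based on a significant mean difference of TAC [24], with 95% confidence level, 80% power", plus 20% for drop-out. No other outcome enters that calculation.

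**The concern.** Which outcomes are primary determines what counts as a positive trial. Here 13 variables have equal standing, so the plan as written does not say which result answers the trial's question. One nominally significant difference among the 13 would fit the stated rule and could be reported as a positive primary outcome.

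The article's own reasoning suggests a ranking that the outcome list does not use. TAC drives the sample size but has no special status. The Background introduces irisin and SIRT1 as markers of mechanism, yet they rank as primary beside HbA1c. The Background also cites two randomized trials of cardamom that found no significant effect on oxidative stress biomarkers, so true null effects within the family are realistic. The Abstract and Discussion promise evidence of efficacy, so the trial is not presented as purely exploratory.

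**Working it through.** **1. Number of primary outcomes** (Primary outcomes section)
- Glycaemic: HbA1c, FBS, insulin = 3
- Lipids: triglyceride, total cholesterol, HDL, LDL = 4
- Oxidative stress: TAC, SOD, GPx, MDA = 4
- SIRT1, irisin = 2
- Total: 3 + 4 + 4 + 2 = 13

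**2. The plan's own figure: 40 per group.** It cannot be recomputed, because the TAC difference and standard deviations are not in the article. It can only be solved backwards. The formula uses a two-sided level (Z at 1−α/2). With equal standard deviations it gives d = (1.960 + 0.842) × √(2/n).
- If 40 already includes 20% loss, n = 40 × 0.8 = 32 evaluable per arm and d = 2.802 × √(2/32) = 0.700.
- If 20% was added on top, n = 33 (33 × 1.2 = 39.6, rounded up to 40) and d = 0.690.

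The effect size of about 0.70 used below is therefore an assumption, not a stated value.

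**3. Chance of at least one p<0.05 if all 13 null hypotheses are true, either direction**
- Independent outcomes: 1 − 0.95^13 = 1 − 0.513 = 0.487.
- Equal correlation between all pairs of test statistics (assumed):

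| Common correlation | Chance of at least one p<0.05 |
|---|---|
| 0 | 48.7% |
| 0.3 | 42% |
| 0.5 | 33% |
| 0.7 | 24% |
| 0.9 | 14% |

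- Correlation in blocks by the four groups in step 1 (assumed): 47% with 0.3 within and 0 between blocks; 41% with 0.5 and 0.2; 32% with 0.8 and 0.3.
- Expected number of false positives: 13 × 0.05 = 0.65 at any correlation.

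**4. Favourable direction only.** Each test then has a 2.5% error rate. Under independence, 1 − 0.975^13 = 1 − 0.720 = 0.280, against 0.025 for a single test.

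**5. Power if all 13 stay primary with strict control.** The first Holm step tests at 0.05/13 = 0.00385, critical z = 2.891. With the assumed d = 0.70 and 32 evaluable per arm:

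| Method | Power at 0.05 | Power at 0.05/13 |
|---|---|---|
| Normal approximation, as in the plan's formula | 80% | Φ(2.802 − 2.891) = 46% |
| Non-central t | 79% | 43% |

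These are lower bounds for Holm, because the threshold for TAC relaxes if other outcomes are rejected first. For 80% power at 0.05/13, n = 2 × (2.891 + 0.842)² / 0.700² gives 57 evaluable per arm, or 57/0.8 = 72 enrolled per arm. With d = 0.690 the figures are 59 and 74.

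**The case against.** Several points on the other side are fair.

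- **Adjustment may be in a document not shown.** Details of multiplicity adjustment are often left to an analysis plan, and the p<0.05 sentence does not rule out adjusted p-values. So the missing adjustment is weak evidence on its own. What remains is the undifferentiated primary list, a protocol-level choice that this article makes explicitly.
- **A reader might infer that the stated 95% confidence is false.** The article does not support that. The 95% belongs to the sample-size calculation for one TAC comparison and holds for that test. No family-wise rate is stated, so none is contradicted.
- **A reader might infer that a false primary result is close to even odds.** That is the independence value, counted in both directions. Total and LDL cholesterol, or FBS and HbA1c, are likely to be correlated, which lowers it. Counting only apparent benefit lowers it further. Even at a common correlation of 0.9, however, the two-sided figure is 14%, still above 5%.
- **The regression might act as an overall test.** It is called multivariate, but the article gives it no gatekeeping role and applies it to all outcome variables in addition to the group comparisons.
- **The list might be read as open-ended.** The open wording attaches to the oxidative stress markers, and the Abstract names the same four. This is editorial.

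**Conclusion.** The concern holds. The protocol fixes 13 equal primary outcomes under one p<0.05 threshold, and its 5% level and 80% power apply to only one of them, which is not singled out. Error over the primary family is therefore not controlled.

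The size depends on correlations that the article does not give. Across common correlations from 0 to 0.7, the chance of at least one false positive in either direction runs from about 49% down to 24%, roughly five to ten times 5%. These figures assume that all 13 nulls are true and that each outcome is tested once. They do not count the second analysis method or the second analysis set. The power figures rest on the back-solved d of about 0.70. The finding itself does not depend on them.

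**What to change.** By a dated, justified amendment made before unblinding:

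1. In the Primary outcomes section, name TAC, the outcome the trial is sized on, as the single primary outcome, tested at two-sided 0.05. The sample-size statement then applies to it unchanged.
2. Make the other 12 outcomes secondary, with Holm- or FDR-adjusted p-values, and state which method is used. Word the oxidative stress markers as a closed list.
3. If all 13 must stay primary, replace the threshold in the Statistical analysis section with Holm-adjusted p<0.05 over the 13. Restate the power: about 43% to 46% for TAC at the first Holm step under the assumed d = 0.70, instead of about 80%.

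Choosing HbA1c or FBS as the primary outcome would need a new power statement, with a difference and standard deviation that the article does not give.

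No new data are needed. The cost is fewer nominally significant results, a less favourable power figure if all 13 are kept, and a documented change to the registered primary outcomes. The article dates registration to 23.11.2016 and describes recruitment in the past tense, so the change may fall after enrolment began. The amendment should say so and confirm that no unblinded data had been seen.
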